23
^ and the PAHO formula.
^
13
^ A recent systematic review and meta-analysis found that estimates of mean population sodium intake from spot urine samples can provide a good indication of overall population salt intake with excellent sensitivity and specificity.
^
20
^

Globally, salt consumption is much higher than recommended. In 2010, global mean sodium intake was 3.95 g/day, with intake in men being approximately 10% higher than in women.
^
24
^ Intakes were highest in East Asia, Central Asia and Eastern Europe and lowest in sub-Saharan Africa and Latin America.
^
24
^ In the United States mean sodium intake was approximately 3.6 g/day and exceeded the recommended daily intake of 2.3 g/day for all age groups except for those 2-3 years old.
^
25
^ Data from the Health of the Nation Study in Barbados showed that mean sodium intake was 2.7 g/day, with intakes higher in men and young people.
^
26
^ Approximately 67% of individuals exceeded the WHO recommended limit of 2.0 g/day.
^
26
^

There are very little data on salt consumption patterns among Jamaicans, but it is generally believed that salt consumption is high. This is due to frequent consumption of salted meats (
*e.g.*, salt fish, salt mackerel, salted pork) in popular local dishes, frequent consumption of canned foods (such as corned beef), and frequent intake of fast foods, which are often high in salt content. Data from the 1990s provide some evidence for high salt consumption in Jamaica. In the Sodium Reduction Trial (SORT), baseline sodium excretion was found to be 149 mEq/day (3,437 mg/day) among a sample of 56 patients.
^
27
^ Additionally, the Spanish Cohort Study reported estimated sodium excretion of 3.3 g/24 hour,
^
28
^ but no recent or national estimates are available. More recently, data from JHLS-III found that among urban participants only 52% were classified as having a low salt diet, defined as no added salt at the table and infrequent consumption of processed foods.
^
29
^

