In keeping with the recommendations of WHO and PAHO and consistent with Caribbean Community (CARICOM) recommendations and a mandate of the Ministry of Health and Wellness in Jamaica, we propose the implementation of a national salt reduction program in order to reduce blood pressure and associated CVD. The program will be aligned with the overall Ministry of Health’s National Strategic and Action Plan for Prevention and Control of Non-Communicable Diseases (NCDs) and the mandate of the Food Industry Task Force. Implementation of a national salt reduction program and achieving the desired effect of reduced blood pressure and associated CVD will require a sequence of actions including the steps included in the WHO SHAKE Technical Package for Salt reduction Program. These strategies include: (i) “measure and monitor salt intake” in the population; (ii) “promote reformulation of foods and meals to contain less salt”; (iii) “implement standards for effective and accurate labelling and marketing of food”; (iv) “educate and communicate to empower individuals to eat less salt”; and (v) creating “support settings to promote healthy eating”.
^
2
^

Jamaica has adopted the global target set by WHO to reduce salt consumption by 30% by 2025. However, Jamaica does not have any baseline data on current salt consumption and therefore would be unable to indicate whether these targets are being met. Additionally, Jamaica does not any available data on salt content in restaurant foods, but a previous study had collected data on sodium content in packaged foods.
^
30
^

The objectives of this study are as follows:
1.
**Objective 1:** To estimate dietary sodium consumption among Jamaicans using spot urinary sodium analyses.2.
**Objective 2:** To assess the use of sodium in the preparation of restaurant foods and estimate the sodium content in restaurant foods.3.
**Objective 3:** To conduct a baseline survey on current knowledge, attitudes, and practices regarding salt intake in Jamaica, and estimate current levels of salt consumption. We will also evaluate associations between knowledge and attitudes regarding salt consumption and actual estimated salt consumption, dietary and other health behaviors, and health characteristics including, blood pressure and body mass index.4.
**Objective 4:** To evaluate the accuracy of spot urine sodium as a measure of dietary sodium intake in the Jamaican setting by comparing estimates to 24-hour urinary sodium excretion.

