^ Mean sodium intake in that study was 2,656 mg per day. Using the ‘
*power onemean’* command in
Stata (RRID:SCR_012763) and 10% margin of error (
*i.e.*, 2,656 vs. 2,390), the effective sample size of 563 gave a power of 97.5%.

*Statistical analyses*

From these data we will estimate mean dietary sodium consumption and the proportion of patients with high dietary sodium consumption. The PAHO formula will be used to estimate 24-hour urine sodium and potassium.
^
23
^

The PAHO formula uses measured spot urine sodium or potassium divided by measured spot urine creatinine multiplied by estimated 24-hour urine creatinine as shown below.
^
32
^
^,^
^
33
^ The 24-hour urine creatinine was estimated using the Chronic Kidney Disease Epidemiology Collaboration (CKD-EPI) formula.
^
32
^
^,^
^
33
^

Equation 1. PAHO formula for 24-hour urine sodium.

$$\left[\text{Estimated}\;24-\text{hour value}=\left(\text{measured spot urine}\;\mathrm{Na}\;\text{or}\;K÷\text{measured spot urine}\;\mathrm{Cr}\right)\times \text{estimated}\;24-\text{hour urinary}\;\mathrm{Cr}\right].$$

Equation 2. CKD-EPI formula for 24-hour urine creatinine.

$$\left[\text{Estimated}\;24-\text{hour urine}\;\mathrm{Cr}=879.89+12.51\times \text{weight}\;\left(\mathrm{kg}\right)-6.19\times \mathrm{age}+\left(34.51\;\text{if black}\right)-\left(379.42\;\text{if female}\right)\right]$$

Note: PAHO, Pan American Health organization; CKD-EPI, Chronic Kidney Disease Epidemiology Collaboration; Cr, creatinine; BMI, body mass index; Na, sodium; K, potassium.

We will also estimate how dietary sodium consumption vary by sex and other sociodemographic factors, self-reported dietary practices, and biomedical characteristics, including blood pressure levels and hypertension awareness. Multivariable regression models will be used to identify factors associated with high sodium intake. Analyses will be weighted to account for survey design.

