*i.e.*, 2,656 vs. 2,457), the required sample size with alpha 0.05 and power 80% was estimated as 511. Given the design effect of 1.94 as calculated above, the minimum sample size accounting for survey design would be 991. We will target a sample size of 1,200 participants (20% above the minimum sample size) to allow for participant non-response and missing data.

*Data management*

Data will be collected by trained data collectors using password-protected tablet computers, with
REDCap (RRID:SCR_003445) data collection software. We will include range and consistency checks to minimize data entry errors. Data collected on the tablets will be protected using data encryption. Options to transfer data to external drives (
*e.g.*, USB flash drives and SD cards will be disabled. Data will then be uploaded to a secure server using data encryption protocols. Deidentified data will then be downloaded for analysis. Access to data will be limited only to members of the study’s data analysis team. De-identified data will be kept indefinitely. Identifiable data, such as consent forms will be kept on secure encrypted servers and will be destroyed by permanent deletion from the server after five years. To assess data accuracy and reliability of data, we will have project staff recollect data from 5–10% of respondents to check against the original collected data.

*Statistical analyses*

From these data we will estimate the proportion of participants reporting appropriate knowledge on the effects of salt on health, and the proportion of participants with various attitudes and practices regarding salt intake. We will also obtain mean urine sodium concentration and estimate 24-hour urine sodium using the PAHO (Equation 1) equations. We will also explore the development of a new equation for use in Jamaica and similar populations from our validation study in ‘

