*Component 4*’, outlined below. We will then estimate the proportion of patients with high dietary sodium consumption. We will also evaluate how dietary sodium consumption, knowledge, attitudes and practices vary by sex, other sociodemographic factors, and biomedical characteristics, including blood pressure levels and hypertension awareness. The analyses for the evaluation of knowledge attitudes and practices will be primarily descriptive, but we will use scores to classify persons in KAP categories. These categories will be created in the analysis phase of the study. Multivariable regression models will be used to identify factors associated with high sodium intake and with good knowledge, attitudes, or practices related to salt intake. Analyses will be weighted to account for survey design.

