After the samples have been collected, we will assess we will assess urine volume, measure urine sodium concentration, urine potassium concentration and urine creatinine. We will exclude participants whose 24 hour urine volume is <500 ml or collection time is <22 hours; we will also exclude participants whose 24 hr urine creatinine is greater than 2SD above or below the sex-specific mean (Du et al 2021). Where collection time is shorter or longer than 24 hours, we will adjust the volume to 24-hours by dividing the total volume by collection time (in hours) and multiplying by 24 (Jackson et al 2020).

*Sample size and power*

Sample size calculations were estimated using the
*‘power onecorrelation’* command in Stata. Estimated correlation coefficients for spot urinary sodium compared to 24-hour urinary sodium were obtained from Brown
*et al.*,
^
23
^ and Tanaka
*et al.*,
^
21
^ using data from Western and Japanese participants in the INTERSALT study. Estimated correlation coefficients were 0.46 for men and 0.34 for women in the study by Brown
*et al.*, and 0.65 for men and women combined in the study by Tanaka
*et al*. Using 0.40 and 0.65 as the null and alternate estimates, yield as sample size of 67. If we went for a slightly more precise estimate of 0.4 and 0.60, the required sample size would be 112 participants. The targeted 120 participants should be adequately powered to assess correlations between spot and 24-hour urine sodium in this study.

*Statistical analyses*

Agreement between different measures of dietary sodium consumption will be computed using the intra-class correlation coefficients and Bland-Altman plots. We will assess whether physical activity level is associated with 24 hour or spot urine sodium and adjust accordingly. We will also classify participants as high salt consumption based on WHO recommended values and assess the level of agreement between classification based on the spot urine sodium and 24-hour urine sodium using the kappa statistics.

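### The share of high sodium consumers is taken from individual spot-urine predictions, so it depends on their spread, and nothing in the plan corrects for this

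*Protocol article*

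**What the plan says.** Component 3, Statistical analyses, will "estimate 24-hour urine sodium using the PAHO (Equation 1) equations" for each participant and may develop a local equation from Component 4. It continues: "We will then estimate the proportion of patients with high dietary sodium consumption". Component 1 likewise plans a mean and a proportion with high consumption from PAHO values, and both components plan regressions: "Multivariable regression models will be used to identify factors associated with high sodium intake". Objective 3 adds associations with "health characteristics including, blood pressure and body mass index".

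The PAHO value is spot sodium over spot creatinine, times an estimated 24-hour creatinine. Of that last term Component 1 says: "The 24-hour urine creatinine was estimated using the Chronic Kidney Disease Epidemiology Collaboration (CKD-EPI) formula". Equation 2 contains weight, age, race and sex.

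The support offered for spot samples is that "estimates of mean population sodium intake from spot urine samples can provide a good indication of overall population salt intake". The same sentence credits them with excellent sensitivity and specificity, but its subject is mean population intake. The individual-level evidence is in the Component 4 sample-size section: spot-to-24-hour correlations of 0.46 (men) and 0.34 (women) in one study and 0.65 in another. Component 4 will report intraclass correlation, Bland-Altman plots and kappa for high versus not high by WHO values, and will calibrate equations that may be used in this study.

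**The concern.** A mean can be estimated well from noisy individual values, because random error averages out. A proportion above a cut-off cannot: it depends on the spread. Predictions that carry spot-sample noise are too dispersed. Predictions from a regression equation are too little dispersed, because they omit the residual variation. The share is right only if the spread of the predictions happens to match that of 24-hour sodium.

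The plan leaves the choice between PAHO and a local equation open, and the two can err in opposite directions. The share of Jamaicans above the limit is a headline baseline figure for the national salt programme, and it could shift by many percentage points with the equation alone. The mean is not exposed to this particular problem.

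A related point concerns the regressions. Weight, age and sex enter the outcome through Equation 2 and are then studied, directly or through BMI, as factors associated with that outcome. If Equation 2 fits this population poorly, the misfit appears as an association.

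**Working it through.** **Inputs.** Mean 2,656 mg/day (Component 1 sample size). Limit 2,000 mg/day, inferred from the WHO limit in the Introduction and the WHO values named in Component 4. Correlation r between spot-based and 24-hour sodium of 0.40 to 0.65. The value 0.40 is the plan's null value and lies between its 0.34 and 0.46. None of these correlations is given for the PAHO formula.

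**SD (assumption).** The document states none. Solving the Component 3 calculation (2,656 vs 2,457, two-sided alpha 0.05, power 80%, n = 511) by the one-sample t-test gives about 1,603. Checks:
- Power at n = 563 for 2,656 vs 2,390 is 97.6% (stated 97.5%).
- 511 × 1.94 = 991, as stated.
- The normal share above 2,000 is Φ(656/1,603) = Φ(0.409) = 65.9%, near the 67% quoted for Barbados.

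**Share above the limit, normal model, 1,603 as the true SD:**
- True: 65.9%.
- Narrow predictions (SD = r × 1,603), share Φ(656/(r × 1,603)): r = 0.40, Φ(1.023) = 84.7%; r = 0.65, Φ(0.630) = 73.6%.
- Over-wide predictions (SD = 1,603/r), share Φ(656 × r/1,603): r = 0.40, Φ(0.164) = 56.5%; r = 0.65, Φ(0.266) = 60.5%.
- At r = 0.34 these become 88.6% and 55.5%.

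If 1,603 is instead the SD of noisy predictions, they show 65.9% and the true share is 73.6-84.7% for the same r.

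**Sensitivity to shape.** The over-wide normal case is crude: Φ(−2,656 × r/1,603) puts 14% (r = 0.65) to 25% (r = 0.40) of values below zero, which PAHO values cannot be. For a lognormal with the same mean and SD:
- Log-variance ln(1 + (1,603/2,656)²), so log-SD 0.557 and median 2,274; true share 59%.
- Over-wide predictions: about 31-56%, depending on whether the mean or the median is kept and on which scale the spread is widened.
- Narrow predictions (log-SD r × 0.557): 64-72% with the median kept, 73-88% with the mean kept.

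**Why kappa does not settle it.** In the normal model with equal spreads, the share is exactly right at 65.9%, yet kappa is only 0.25 (r = 0.40) to 0.44 (r = 0.65). Kappa measures individual agreement; it does not correct the marginal share.

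**Why the proposed correction works.** For narrow predictions the residual SD is 1,603 × √(1 − r²): 1,469 at r = 0.40. Averaging individual exceedance probabilities restores the total spread, √(641² + 1,469²) = 1,603, and hence 65.9%.

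**Equation 2 (Black, age 45).** Man 80 kg: 879.89 + 12.51 × 80 − 6.19 × 45 + 34.51 = 1,636.7. Woman 80 kg: 1,257.2, ratio 0.768. Man 100 kg vs 60 kg: 1,886.9/1,386.5 = 1.361. At the same spot Na/Cr, the formula itself therefore makes the woman's estimate 23% lower than the man's and the heavier man's 36% higher than the lighter man's.

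**The case against.** The strongest reply is that Component 4 exists to test this classification, and that the protocol states only that a proportion will be estimated, not how; the estimator could be left to the analysis plan. It stands in part: the predictions are not used without validation, and the local equation is optional and its form unspecified, so the narrow-prediction figures apply only if such a regression is adopted. But Component 4 itself classifies individuals from their spot-based values, the natural reading of Component 3 is the same, and no sentence feeds the validation results back into the proportion.

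The second reply is that the figures rest on a back-solved SD, correlations from other formulae and a normal model that fails in the noisy case. This stands. A reader might infer that the plan's share will be too low, or always pulled towards 50%. The document does not support that: a lognormal with its mean kept falls below 50%, and which kind of dispersion dominates is unknown.

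The third concerns associations. A reader might infer from the 23% and 36% contrasts that links with sex and weight will be spurious, and that log spot Na/Cr should be modelled instead. Neither follows. Equal Na/Cr is not equal sodium intake, because creatinine excretion itself varies with sex and body size; Equation 2 is there to adjust for that. On its own figures, a man and a woman of 80 kg with identical 24-hour sodium would differ by 30% in Na/Cr (1,636.7/1,257.2), the woman higher. The contrasts show dependence on the formula, not bias, and the document gives no evidence of misfit.

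**Conclusion.** The concern holds in limited form. The share of high consumers in Components 1 and 3 rests on individual predictions that the document supports only at the level of the mean, and no planned step corrects it for over- or under-dispersion. Under the stated assumptions the error could be about 5 to 9 percentage points downwards (66% to 57-61%) or 8 to 19 upwards (66% to 74-85%). These figures illustrate the possible scale and are not forecasts; the actual size and sign must come from the Component 4 data. For the regressions, the supported conclusion is that sex, age and BMI contrasts depend on how well Equation 2 fits Jamaicans, which is untested but testable within the study. The change should be made; it does not call the mean intake estimate or the sample-size arithmetic into question.

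**What to change.** - **Component 3 prevalence.** Use the paired Component 4 data to estimate the distribution of 24-hour sodium given the spot-based prediction, on a suitable scale such as the log. Compute each participant's probability of exceeding the limit and report the survey-weighted mean, alongside or instead of the count of point predictions. State the limit. Carry the uncertainty from about 120 pairs into the interval: with normal residuals and ignoring clustering, the residual SD alone has a relative standard error near 1/√(2 × 118) = 6.5%.
- **Component 1 prevalence.** Label the PAHO-based share as uncorrected, or apply the Component 4 correction as a sensitivity analysis. State the transport assumption: an earlier survey, from age 15 rather than 18. Its analysis is already under way, so this should be settled first.
- **Associations.** Check Equation 2 against the measured 24-hour creatinine, which Component 4 already plans to obtain, by sex, age and weight. Recalibrate if it misfits, and report sex, age and BMI contrasts as formula-dependent. Do not substitute log Na/Cr to answer the sex and weight questions.

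The cost is analysis code and a longer explanation; no new measurements are needed. The price is a distributional assumption, and reliance on a residual spread from participants in essentially the first six enumeration districts applying to the whole sample. Both should be stated.

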## Discussion

This study will provide important baseline data on salt consumption in Jamaica and will fulfil interventions recommended in the first component of the WHO SHAKE Technical Package for Salt Reduction. The findings will serve as a guide to Jamaica’s Ministry of Health and Wellness in the development of a national salt reduction program. Findings will also inform interventions to promote individual and population level sodium reduction strategies as the country seeks to achieve the national target of a 30% reduction in salt consumption by 2025.

This study has some limitations. Given the limited funds available for the study, we have constrained the sample size of ‘
*Component 3*’ to 1,200 individuals. While this will provide reasonable power for our main study question, estimates for subgroups with the population may be imprecise and our ability to identify associations between salt intake and some characteristics may be limited. We also anticipate that some restaurant owners may be unwilling to share information on ingredient quantities/recipes and as such some of these estimates may be based on usual practice by our nutritionist. Additionally, it would have been useful to measure salt content in food samples for the restaurants, but we do not have funding for this. We intend to seek funding to perform such measurements in future studies. For component 4, we did not collect information on lean meat intake and therefore will not be able to assess how this relates to 24-hour urine sodium.

The strengths of this study include the use of a nationally representative population-based sample, thus ensuring that the findings will be generalizable to the Jamaican population. The multi-component structure of this study will ensure that we address several important questions related to salt and health in the Jamaican context. The broad team on investigators and the joint effort between the Ministry of Health and Wellness and the University of the West Indies will ensure that the findings are taken up and translated into policy.

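### Component 3 models 'good' knowledge, attitudes or practices as a category cut from a score, which costs the outcome models about 36–51% of the score's information if 'good' is a two-level outcome

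*Protocol article*

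**What the plan says.** The Statistical analyses paragraph of Component 3 sets out the handling of the KAP data in three steps.

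- It gives the general character: "The analyses for the evaluation of knowledge attitudes and practices will be primarily descriptive".
- It then says "we will use scores to classify persons in KAP categories", and adds "These categories will be created in the analysis phase of the study".
- It commits to multivariable regression to "identify factors associated with high sodium intake and with good knowledge, attitudes, or practices related to salt intake".

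Neither the number of categories nor any cut-off is given, and no model of the uncut score is described. High sodium intake is different: the Introduction and Component 4 refer to a WHO recommended value.

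Objective 3 in the Introduction includes an association aim: "We will also evaluate associations between knowledge and attitudes regarding salt consumption and actual estimated salt consumption", together with health behaviours, blood pressure and body mass index. It does not say how knowledge and attitudes are to be coded there.

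**The concern.** A numeric score is built, cut into groups, and the group labelled 'good' becomes the regression outcome. People just above and just below the cut are treated as opposites, and everyone on the same side is treated as identical. Without an external threshold that gives the cut a meaning of its own, that information is given up for nothing except simpler presentation.

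What is at stake is power and precision in the models that look for factors related to KAP. The sample is fixed at 1,200 by funding, so information lost through coding cannot be bought back with more participants. A factor truly related to knowledge could appear unrelated because of the cut, and the results are meant to guide salt-reduction interventions.

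**Working it through.** **The plan's own figures.** The article gives no figure for KAP associations. Its sample size is for mean sodium, and that calculation reproduces. The SD is not stated. The value implied by Component 1 (97.5% power at n = 563 for 2,656 against 2,390 mg/day) is about 1,607 mg/day. With that SD, 2,656 against 2,457 at 80% power and two-sided 5% needs 514, against the stated 511. Then 511 × 1.94 = 991, and 1,200/991 = 1.21.

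**Inputs for the check.** From the article: target 1,200 and design effect 1.94. Assumed: a roughly normal score, a linear relation, and a two-sided 5% test.

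**Information kept after a cut.** For a normal score with share p classed 'good' and cut-point c, the share of information kept is φ(c)²/[p(1 − p)].

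| Coding | Calculation | Kept | Lost |
|---|---|---|---|
| 50/50 | 0.3989²/0.25 | 64% | 36% |
| 30/70 | 0.3477²/0.21 | 58% | 42% |
| 20/80 | 0.2800²/0.16 | 49% | 51% |
| Three equal ordered groups, trend | 2 × 0.3636²/(1/3) | 79% | 21% |
| Four equal ordered groups, trend | same principle | 86% | 14% |

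**Illustrative power.** Effective n = 1,200/1.94 = 619. Power ≈ Φ(atanh(r′) × √(n − 3) − 1.96), where r′ is the correlation on the score times the square root of the share kept. The value r = 0.113 is chosen because it gives 80% power on the full score.

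- Full score: 0.1135 × 24.81 = 2.82; 2.82 − 1.96 = 0.86; power 80%.
- Median split: r′ = 0.113 × 0.798 = 0.090; 2.24 − 1.96 = 0.28; power 61%.
- 20/80 split: r′ = 0.113 × 0.700 = 0.079; 1.97 − 1.96 = 0.01; power 50%.
- Tertile trend: r′ = 0.113 × 0.891 = 0.101; 2.51 − 1.96 = 0.55; power 71%.

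In sample-size terms, 619 becomes about 394 (619 × 0.637), 303 (619 × 0.490) and 491 (619 × 0.793).

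**Simulation.** With 1,500 data sets of 619, linear regression on the score had 80% power, logistic regression on the median split 61%, and logistic regression on the 20/80 split 50%.

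**Sensitivity to score shape.** Simulated scores of 5, 10 and 20 items, cut so that 42% to 63% were 'good', kept 66% to 70% of the information. With 13% to 14% 'good' they kept 34% to 36%.

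**The case against.** The strongest reply is that these analyses are called mainly descriptive, the survey was sized for mean sodium, and estimating the proportion with appropriate knowledge is a stated aim. Asking who has good knowledge follows naturally from that aim and suits a Ministry audience. This lowers the weight of the point but does not remove it, because the same paragraph commits to multivariable models of 'good' KAP.

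Four stronger readings are tempting, and the article does not support them.

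- A reader might infer that the scores are used only to form categories. The article does not say so. It also plans to look at how KAP varies by sex and other characteristics, without stating the coding.
- A reader might infer that KAP is also cut when it is the exposure, so that a null result for knowledge against salt intake would be an artefact. Categories are the only KAP form described, but 'good' KAP is named only as an outcome. The coding in models for sodium, blood pressure or body mass index is not given and may be settled in a fuller document.
- A reader might quote a flat loss of 20% to 50%. The lower end needs about three ordered groups analysed as a trend, which does not fit a two-level 'good' outcome.
- A reader might take the Discussion's admission that "our ability to identify associations between salt intake and some characteristics may be limited" as a comment on KAP scoring. It concerns salt intake and the limited sample; it shows only that power for associations is already tight.

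The numerical caveats also stand. The score's length and distribution are not given, and r = 0.113 is illustrative. The design effect was derived for mean urinary sodium in a survey of 171 enumeration districts; Component 3 uses 60, and the value for a KAP regression coefficient may differ. That affects the power figures but not the percentage of information lost. If the true relation were a step at the cut, cutting there need not lose information. The questionnaire was adapted from published instruments, so a scoring convention may exist that the article does not show.

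**Conclusion.** The point holds for the 'good' KAP outcome models. As written, they use a categorised score with no cited threshold and no full-scale analysis alongside.

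Under a roughly normal score, a linear relation and a two-level outcome, the loss is about 36% to 51% of the information for splits between 50/50 and 20/80. It is nearer 30% for a short discrete score cut near the middle, and about 21% if three equal ordered groups are analysed as a trend. The drop in power from 80% to 61% or 50% is an illustration at an effective sample of 619, not a prediction.

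No loss is demonstrated for analyses with KAP as an exposure, and the sodium estimates are untouched. Leaving the cut-points to the analysis phase is a separate matter: the loss shown here would remain if they were fixed beforehand.

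**What to change.** In the Component 3 Statistical analyses paragraph, state that:

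- the multivariable KAP models use the knowledge, attitude and practice scores on their full scale, by survey-weighted linear or ordinal regression;
- any Objective 3 model with knowledge or attitudes as the exposure enters the score on its full scale, with a check for non-linearity such as a spline or quadratic term;
- the KAP categories serve the prevalence tables and, if wanted for policy readers, a secondary model of 'good' KAP.

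This changes analysis wording only. Field work has begun, but the categories are still to be created, so the change remains open and needs no new data or participants. The small downside is that a difference in score is less direct for policy readers than an odds ratio for 'good' KAP; the retained categories meet that need.

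### The only named multivariable models of sodium are worded for high intake, most naturally a yes/no outcome; if fitted that way, they lose about 41% of the information at the share above the limit quoted for Barbados.

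*Protocol article*

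**What the plan says.** Under Statistical analyses for Component 3 the protocol states that "Multivariable regression models will be used to identify factors associated with high sodium intake". Component 1 uses the same words. Neither place gives a model type or an outcome coding.

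Three things bear on what high means:

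- Earlier in the Component 3 text it is a proportion: "We will then estimate the proportion of patients with high dietary sodium consumption".
- In Component 4 it is a classification: the authors will "classify participants as high salt consumption based on WHO recommended values".
- The Component 3 sentence that announces the models pairs high intake with good knowledge, attitudes or practices, after saying that scores will be used to place people in categories.

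Sodium as a quantity also appears. Component 3 says: "We will also evaluate how dietary sodium consumption, knowledge, attitudes and practices vary by sex, other sociodemographic factors, and biomedical characteristics". Neither the scale nor any adjustment is given for that analysis. Objective 3 in the Introduction is worded in terms of estimated salt consumption, not of exceeding a limit. The Discussion concedes that "our ability to identify associations between salt intake and some characteristics may be limited".

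**The concern.** Estimated 24-hour sodium is continuous. A yes/no outcome treats people just either side of the limit as different and everyone well above it as alike. The adjusted associations of sodium with knowledge, attitudes, diet and blood pressure would then be estimated less precisely than the same data allow. The protocol already expects limited ability to find such associations because funding constrained the sample, so the choice of outcome scale in the adjusted models matters more than usual. A real association could be missed, or reported with a needlessly wide interval, for a reason unrelated to the sample size.

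**Working it through.** **Inputs from the protocol**

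- Share above the limit (Introduction, Barbados): "Approximately 67% of individuals exceeded the WHO recommended limit of 2.0 g/day".
- Planning mean (Component 1): "Mean sodium intake in that study was 2,656 mg per day".
- Component 1 power: 97.5% with 563 effective participants for 2,656 vs 2,390, a difference of 266 mg/day.
- Component 3 sample size, for 2,656 vs 2,457, a difference of 199 mg/day: "the required sample size with alpha 0.05 and power 80% was estimated as 511".
- Design effect 1.94, giving a minimum of 991.

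The protocol gives no SD and no figure for the regression models.

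**Reproducing the plan's figure.** Solving the one-sample t-test power for Component 1 (two-sided alpha 0.05 assumed) gives an SD of about 1,607 mg/day. Put into Component 3, n ≈ ((1.960 + 0.842) × 1,607 / 199)² ≈ 512, or 514 with the t distribution, against the stated 511. Then 511 × 1.94 = 991.3. The planning figures agree with one another, and all of them concern a continuous mean.

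**Information kept by a yes/no outcome.** For a normal outcome with small shifts in location, the efficiency of an above/below analysis relative to the continuous one is

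RE = φ(z_p)² / [p(1 − p)],

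where p is the share above the cut, z_p the normal quantile of p and φ the normal density. At p = 0.67, z_p = 0.440 and φ = 0.362, so RE = 0.1312 / 0.2211 = 0.593, a loss of 41%.

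| Share above cut | RE | Loss |
|---|---|---|
| 50% | 0.637 | 36% |
| 60% | 0.622 | 38% |
| 67% | 0.593 | 41% |
| 75% | 0.539 | 46% |
| 80% | 0.490 | 51% |

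The smallest possible loss is the 36% at an even split. The formula needs only p, so it holds equally if log sodium is the normal variable.

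**Cross-check from the mean and SD.** With mean 2,656 and SD 1,607, the share above 2,000 mg is 65.8% if normal (z = (2,000 − 2,656)/1,607 = −0.408; RE 0.599; loss 40%) and 59% if log-normal (RE 0.625; loss 38%). The normal version puts about 5% of people below zero (2,656/1,607 = 1.65 SDs), so a log scale is the more credible one. The conclusion barely moves.

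**What it does to power.** A contrast with 80% power on the continuous scale has an expected test statistic of 1.960 + 0.842 = 2.802. As yes/no at RE 0.593 this becomes 2.802 × √0.593 = 2.158, and power is Φ(2.158 − 1.960) = Φ(0.198) ≈ 58%. This does not depend on the sample size. A simulation with log-normal data, 67% above the cut and 309 per group gave 80% power on log sodium, 73% on raw sodium and 58% as yes/no.

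**The case against.** The protocol does not say that the outcome is dichotomised. The WHO limit is tied to classifying participants only in Component 4, for the kappa statistic, and a condensed article may leave model form to a fuller document. That stands as a limit on certainty: yes/no is inferred. It does not dispose of the point. The article does name the outcome, twice, and if a linear model is meant, the wording is misleading and should still change.

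A reader might also infer that the study throws away 40% of its information on sodium. The documents do not support that. Objective 3 and the Component 1 and 3 analysis paragraphs plan to examine sodium consumption itself, and Component 3 plans to compare urine sodium excretion by hypertension and diuretic use, with models including and excluding people on diuretics. What is not spelled out is an adjusted model of continuous sodium for the listed factors.

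Nor is the threshold model worthless. Exceeding the WHO limit is a question of its own for a national salt programme.

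Finally, it is tempting to turn the loss into an effective sample by dividing 1,200 by 1.94 and discounting the result. That assumes full response, although the margin above 991 is there for non-response and missing data. It also assumes that a design effect calculated from urinary sodium values carries over to regression coefficients. Neither is shown.

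The Discussion's admission concerns sample size, not outcome coding. It shows that precision for associations is scarce, nothing more.

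**Conclusion.** The point holds in a conditional form. As worded, the only named multivariable models of sodium have high intake as their outcome, while Objective 3 concerns estimated consumption. Fitted as yes/no, those models lose about 41% of the information at 67% above 2.0 g/day, and about 36% to 51% for shares from 50% to 80%. This rests on an approximately normal or log-normal outcome, associations that act as a modest shift in location, and a cut at the WHO limit. The Jamaican share above the cut is unknown, and 67% is borrowed from Barbados. The loss is one of precision in the adjusted models; it does not make any planned estimate invalid. It is a worthwhile improvement rather than an error that threatens the study.

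**What to change.** In the Statistical analyses text of Components 1 and 3, state that adjusted associations with sodium will be assessed by survey-weighted multivariable linear regression on continuous estimated 24-hour sodium, for example on the log scale. Keep a multivariable model for intake above the WHO limit alongside it as a policy-facing result, and state the cut-point there. The cost is one extra model per component, with no new data, measurements or participants. Component 1 is already being analysed and Component 3 is in the field, so the wording is best settled before the models are run.
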